## Methods

The FFAKI trial is a multicentre, randomised, site-stratified, clinical pilot trial with adequate computer generation of the allocation sequence with permuted blocks of varying size and allocation concealment. Randomisation is performed using sequentially numbered, opaque, sealed envelopes.

The trial statistician is blinded but due to the nature of the intervention it is not possible to blind patients or caregivers.

The trial is initiated at three separate centres in Denmark. Each centre has one or two primary investigators with expert knowledge in the FFAKI intervention and protocol. Participants in the FFAKI trial will receive protocol-specific treatment during their entire ICU stay. Therefore, every caregiver at participating centres receives training in the protocol by either the principal investigator or one of the primary investigators. It is expected that the primary centre (Nordsjællands Hospital) will include 20–30 patients and each secondary centre will include 10–15 patients.

The trial protocol was written according to the Standard Protocol Items: Recommendations for Interventional Trials (SPIRIT) Statement [12]. A populated SPIRIT Checklist and figure are provided in Additional file 1 and Fig. 1, respectively.

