### Resuscitation

During the entire trial, the physiologic response to fluid removal is monitored with three variables indicating inadequate circulation. These are:Mottling beyond the edge of the kneecaps [14]Hypotension (MAP <50 mmHg) resistant to inotropes and vasopressorsPlasma lactate ≥4 mmol/L [15]

Mottling and MAP are monitored continuously and lactate is routinely measured four to six times each day and on clinical indication.

If one or more signs of inadequate circulation are present the resuscitation algorithm is started:Pause fluid removalGive a crystalloid fluid bolus of 250–500 mLRe-evaluate circulatory status within 30 minRepeat fluid therapy and revaluation until adequate circulation (lactate <4 mmol/L, MAP >50 mmHg and no mottling beyond kneecaps) have been maintained for minimum 1 hRestart fluid removal in 25% reduced dose for a minimum of 4 h before evaluating effect

Fluid removal is continued until the patient achieves neutral cumulative fluid balance (±1000 mL), which is then attempted maintained for the entire duration of ICU admission.

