### Statistical analysis

The main objective of the FFAKI trial is to determine whether the trial intervention is feasible. To capture this we have decided to examine whether the trial intervention leads to a clinically relevant difference in fluid balance after 5 days. This is treated as an interim outcome and in accordance with the newly published Consolidated Standards of Reporting Trials (CONSORT) extension to randomised pilot and feasibility trials [16], we used the standard method of calculating sample size. By including 50 patients in the trial we will have the power to show a difference of 6 L in cumulative fluid balance between groups with a *β* value of 0.80 and a two-sided *α* value of 0.05. The sample size estimation is based upon observational data of patients fulfilling the FFAKI inclusion criteria admitted at our ICU in 2012 and 2013 (mean fluid balance 13.8 L, standard deviation (SD) 7.4 L).

Two complimentary analyses of the primary outcome will be performed in order to account for attrition due to death. In the first analysis the subject-specific fluid balances are modelled in a ‘linear random-effects model’ unconditional on survival status. Difference in fluid balance 5 days after randomisation will be assessed using a Wald test. In the second analysis we will estimate the ‘survival average causal effect’ of the intervention using principal stratification and include a sensitivity analysis to assess the influence of possible violations of assumptions. In both models missing data due to dropout will be handled using ‘inverse probability weighting’.

All parametric data will be presented as mean (SD) and compared using Student’s *t* test. Nonparametric data will be reported as median (interquartile range (IQR)) and compared using the Mann-Whitney *U* test.

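### Free improvement: use Welch's rather than Student's t test for the two secondary fluid-balance outcomes, because only one arm is treated toward a common target and the arm variances may well differ

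*Protocol article*

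**What the plan says.** The last paragraph of the Statistical analysis section sets a general rule: "All parametric data will be presented as mean (SD) and compared using" Student's t test. Data judged nonparametric get the Mann-Whitney U test. No unequal-variance version of the t test is named.

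The primary outcome, cumulative balance 5 days after randomisation, is handled separately in the same section. It has a linear random-effects model with a Wald test, and a survival average causal effect by principal stratification. The general rule therefore applies to the remaining continuous outcomes. In Table 1 the fluid-balance outcomes among these are mean daily balance during the ICU stay and cumulative balance over the whole ICU stay.

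The Resuscitation section gives the experimental arm a common end point: "Fluid removal is continued until the patient achieves neutral cumulative fluid balance (±1000 mL), which is then attempted maintained" until ICU discharge. The Standard care section leaves fluid giving and removal in the control arm to the treating clinicians.

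The sample size rests on a single SD from observational patients: "mean fluid balance 13.8 L, standard deviation (SD) 7.4 L". Methods describes the design as "randomised, site-stratified, clinical pilot trial with adequate computer generation of the allocation sequence with permuted blocks of varying size". It adds: "The trial is initiated at three separate centres in Denmark". The allocation ratio is not stated; 1:1 is assumed below.

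**The concern.** Student's t test pools the two sample variances. If the true variances differ, the pooled standard error is right on average only when the arms have equal numbers. When the arm with the smaller spread is the larger one, the standard error is too small, so the test rejects too often and the interval is too narrow. When that arm is the smaller one, the opposite happens.

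The protocol gives a reason to expect a difference in spread. Treating one arm to a shared target tends to draw its values together, and the other arm has no such target. Any narrowing should be most plausible over the whole ICU stay, where there is most time to reach and hold neutral balance, and that is the period of both secondary outcomes.

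Arms of unequal size are also realistic. Blocks may be left incomplete at three sites with 50 patients in all, and data may be missing. Which arm will be smaller cannot be known in advance, so neither can the direction of the error. At stake is whether the p-values and 95% intervals for these two outcomes have their stated level.

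**Working it through.** **1. The plan's own figure.** The article says: "By including 50 patients in the trial we will have the power to show a difference of 6 L in cumulative fluid balance between groups". Its inputs are a difference of 6 L, SD 7.4 L, two-sided α 0.05 and power 0.80 (printed as a β value, but it is the power).

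- Normal formula: n per arm = 2 × (1.960 + 0.842)² × 7.4² / 6² = 2 × 7.85 × 54.76 / 36 = 23.9, so 24 per arm and 48 in total.
- Exact t-test power with equal SDs: 0.785 at 24 per arm and 0.802 at 25 per arm.

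The stated 50 is reproduced. This calculation uses one common SD.

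**2. Why the split matters.** Let E be experimental and C control.

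- True variance of the mean difference: s_E²/n_E + s_C²/n_C.
- What the pooled test estimates on average: [(n_E − 1)s_E² + (n_C − 1)s_C²] / (n_E + n_C − 2) × (1/n_E + 1/n_C).

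Take s_C = 7.4 L (planning SD) and s_E = 3.7 L (assumed, half of it):

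- **25/25.** Both expressions give (13.69 + 54.76)/25 = 2.738, a standard error of 1.65 L. Only the degrees of freedom are off: 48 for Student against about 35 for Welch.
- **27 E / 23 C.** True: 13.69/27 + 54.76/23 = 2.888, SE 1.70 L. Pooled: (26 × 13.69 + 22 × 54.76)/48 × (1/27 + 1/23) = 2.618, SE 1.62 L. The pooled SE is about 5% too small.
- **23 E / 27 C.** True: 13.69/23 + 54.76/27 = 2.623, SE 1.62 L. Pooled: 2.893, SE 1.70 L. The pooled SE is about 5% too large.

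**3. Size of the test.** Simulation with normal data, 400,000 replicates per setting, control SD 7.4 L, nominal two-sided 0.05, Student's test:

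| Experimental SD (assumed) | 25 E / 25 C | 27 E / 23 C | 23 E / 27 C |
|---|---|---|---|
| 7.4 L (equal) | 0.050 | 0.050 | 0.050 |
| 5 L | 0.050 | 0.058 | 0.044 |
| 3.7 L | 0.052 | 0.064 | 0.041 |
| 2 L | 0.055 | 0.072 | 0.039 |
| 1 L | 0.056 | 0.075 | 0.039 |

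Welch's test lay between 0.049 and 0.051 in every setting. For a given split, the size depends only on the ratio of the SDs, so the table also serves mean daily balance, which is on another scale.

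Larger errors need larger imbalance. With experimental SDs of 5 down to 1 L, Student's size is 0.070-0.116 at 30 E / 20 C and 0.036-0.020 at 20 E / 30 C.

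**4. A non-normal case.** Assume that 70% of experimental patients lie uniformly within ±1 L and the rest follow a normal distribution with mean 9 L and SD 6 L (overall SD 5.3 L), against a control SD of 7.4 L. Over 100,000 replicates per split, Student's 95% interval covers 94.8% at 25/25, 94.2% at 27 E / 23 C and 95.4% at 23 E / 27 C. Welch's covers 94.9-95.0%.

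**5. Price of Welch if the SDs are equal.** Power for 6 L with both SDs at 7.4 L is 0.802 (Student) and 0.801 (Welch) at 25/25, and 0.786 and 0.782 at 30/20.

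**The case against.** **The result that matters most is not analysed by t test.** This stands. A reader might infer that the interval for the day-5 difference, the main product of the pilot, is mis-sized. The documents do not support that, because the primary outcome has a Wald test from a random-effects model and a survivor average causal effect. Nor can the same weakness be attributed to the random-effects model: its variance structure is not described, and an article may leave that to the full protocol or analysis plan.

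**The experimental arm is not fixed within 1 L of neutral.** This also stands. The target is attempted, and removal is paused and fluid given when circulation is inadequate. The working goal is a rate of at least 1 mL/kg/h, which mainly shifts balances until neutral is reached. At exactly that rate, 120 h removes 7.2-12.0 L for an assumed weight of 60-100 kg. If 13.8 L is taken as a starting balance (an assumption), 1.8-6.6 L would remain on day 5. Uneven tolerance could even widen the spread. All this makes the size of the variance difference uncertain, and its direction too. It gives no support to assuming equality, and Welch's test is valid in either direction.

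**A true null with halved spread is implausible, because the intervention must move the mean.** This is fair for the type I error, but it does not remove the point. For normal data the coverage of the interval is one minus the size whatever the true difference. A size of 0.064 therefore means 93.6% coverage.

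**Blocked randomisation keeps the arms close, and both outcomes can be computed for patients who die in the ICU.** Agreed. This is why the effect is small.

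**Student's t test is a conventional choice, and such detail belongs in the analysis plan.** The article does not leave the choice open, since it names the test. That makes the point a preferable method rather than an error or a contradiction.

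**Conclusion.** The point holds as a free improvement of small size, confined to mean daily fluid balance and cumulative balance over the ICU stay, and only if these are treated as parametric. With a smaller experimental SD, Student's test is close to nominal at equal numbers (5.0-5.6%). It is somewhat liberal with 27 experimental and 23 control patients (5.8-7.5%) and somewhat conservative with the reverse split (3.9-4.4%). Welch's test holds its level throughout.

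These figures rest on normal data, 1:1 allocation, the planning SD of 7.4 L for controls, and an assumed experimental SD of 1 to 5 L. The documents give no SD by arm. If the SDs are equal, Student's test is correct at every split. The sample size of 50 reproduces and is unaffected, as is the primary analysis.

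**What to change.** In the Statistical analysis section, name Welch's t test in place of Student's for the comparisons of mean daily fluid balance and of cumulative balance over the ICU stay. For each, report the mean difference in litres (litres per day for the daily mean) with its Welch 95% interval.

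The cost is a change of wording and a software option. No patients, data or visits are added. If the variances turn out equal, the power lost is about 0.1 percentage points at 25/25 and 0.3 at 30/20.

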## Discussion

The FFAKI trial consists of a complex intervention that alters the core of current therapy for critically ill patients. Furthermore, the intervention is designed to treat an iatrogenic condition (fluid overload). To our knowledge there are no previous implementations of forced fluid removal in a randomised clinical design and we have identified several key areas in which a trial of forced fluid removal might prove unfeasible:Patient physiology might not allow early and forced fluid removalPatients who develop AKI and fluid overload are characterised by severe critical illness, often with failure of multiple organ systems and they receive a multitude of interventions including mechanical ventilation, fluid therapy, antibiotics, vasopressors, inotropes and dialysis. The underlying condition further compromises the physiology of the patient leading to leaky capillaries and loss of intravascular albumin [17]. Fluid removal by diuretics or CRRT is done from the intravascular compartment and the extracorporeal removal of fluids depends upon the compensatory movement of fluids from the extravascular compartment to the intravascular compartment [11]. These factors might oppose removal of fluids and patients who undergo forced fluid removal could develop further worsening of circulatory status leading to discontinuation of fluid removal according to the safety parameters described earlier. Previous trials have suggested that fluid restriction and fluid removal in critical illness is safe and well tolerated by patients admitted to the ICU. The FACCT trial [18] showed a difference in fluid balance of 7 L with restricted fluid therapy in patients with acute lung injury. Ganter and co-workers performed fluid removal in 10 critically ill patients with a mixed medical history [19] and achieved very large cumulative volumes of fluid removal ranging from 7.4 to 19.8 L during the course of 72 h
2.The Hawthorne effect might alter the administration of IV fluids leading to reduced incidence of fluid overload and abolish the need for forced fluid removalFluid overload is an iatrogenic condition that arises as a consequence of the current practice of fluid therapy in critical illness. When a trial of forced fluid removal is initiated there will be an inevitable increased focus on the indications for fluid administration and removal. This produces a risk of a Hawthorne effect leading to less fluid administered by clinicians which would reduce the incidence of fluid overload in the given patient population and abolish the need for a trial of this nature
3.Heterogeneity of the patient population could dilute any potential effect of the intervention leading to reduced power and the need for a very large sample sizeThe baseline chance of recovering renal function following AKI in the ICU varies with age, gender and the severity of kidney injury. Patients who have a high chance of recovering with the current standard of care will have very little potential benefit of participating in a trial of new therapeutic interventions. Furthermore, these patients could dilute the potential effect of a given intervention and lead to a loss in power and need for larger sample sizes. We have recently developed a model to predict the chance of recovering renal function following AKI in the ICU, which is called the ‘Renal Recovery Score’ (RRS) (not yet published). In the development and validation of the model we found that the 20% of patients with the highest chance of recovering renal function had a RRS value of >64% and an 80–85% frequency of recovery. To selectively include patients with a moderate to high risk of persistent renal injury we will be using a RRS value of <60% as part of the inclusion criteria
4.Lack of blindingDue to the nature of the intervention it is not possible to blind participants, caregivers administering the intervention or caregivers administering co-interventions. This introduces a risk of bias which we will evaluate with fluid therapy and dialysis data in both treatment arms. To avoid overly aggressive fluid removal in the control group we discourage the use of dialysis unless specifically indicated according to previously described criteria
5.Lack of protocol adherenceForced fluid removal in critically ill patients with continued need for vasopressors and inotropes might seem controversial to some clinicians and it is uncertain whether our intervention can be performed with the acceptance of the treating clinicians. Therefore, we register the frequency of protocol violations defined as the use of dialysis outside the recommended indications in the control group, and cessation of fluid removal before fulfilment of safety criteria or achievement of neutral fluid balance in the experimental group

By performing a pilot trial with a primary outcome of fluid balance 5 days after randomisation we will be able to evaluate whether the intervention is feasible. Furthermore we will know if it leads to a clinically relevant difference in fluid balance which would indicate that implementation of this protocol in a larger sample size would provide analysable results regarding a causal relationship between fluid removal and patient-centred outcomes of renal recovery and survival.

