**Fig. 5 Fig5:**
[figure not shown]
FFAKI resuscitation algorithm

The experimental intervention is guided by a therapeutic goal of average net negative fluid balance ≥1 mL/kg/h and safety variables indicating inadequate circulation (lactate ≥4 mmol/L or mean arterial pressure (MAP) <50 mmHg or mottling beyond the edge of the kneecaps).

The therapeutic effect is evaluated at three daily summary points on the ICU observation charts (06:00, 14:00 and 22:00), while safety variables are evaluated continuously.

The first choice for fluid removal is diuretic therapy with furosemide which is continued for a minimum of 8 h. If the therapeutic goal cannot be achieved and maintained by diuretic therapy it is replaced by fluid removal with continuous renal replacement therapy (CRRT).

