### Standard care

In the control group receiving standard care, there are no protocolled interventions. Fluid administration and removal is done at the discretion of the treating clinicians. Use of dialysis is encouraged only in the presence of severe disturbances in fluid, electrolyte and acid-base balance:Hyperkalaemia (p-K^+^ >6 mmol/L)Severe metabolic acidosis attributable to AKI (pH <7.25 and standard base excess (SBE) below −10 mmol/L) resistant to intravenously (IV) administered bicarbonate infusionSevere respiratory failure with PaO^2^/FiO^2^ < 13 kPa and bilateral infiltrates/oedema on the chest X-rayAside from these absolute indications, RRT may be provided in case of progressive azotaemia and blood urea (BUN) >25 mmol/L

All data are collected in a paper-based Case Research Form (CRF) and participants are followed for a total of 90 days. The primary outcome of the FFAKI trial is cumulative fluid balance 5 days after randomisation. All outcome variables are shown in Table 1. Furthermore, we will evaluate the safety of the intervention by registering known serious adverse reactions (SARs) to furosemide and serious adverse events (SAEs) to fluid removal including: arrhythmia, ischaemia, vasopressor use and progression of organ failure as captured in the daily Sequential Organ Failure Score (SOFA) score.

**Table 1 Tab1:** Primary, secondary and exploratory outcomes for the FFAKI trial

Primary outcome	Cumulative fluid balance 5 days after randomisation
Secondary outcomes	Mean daily fluid balance during ICU stay
	Cumulative fluid balance during the entire ICU stay
	Time to neutral cumulative fluid balance
	Number of patients with one or more major protocol violations
	Accumulated SARs in each intervention arm during the ICU stay
Exploratory outcomes	All-cause mortality at day 90
	Days alive and out of hospital within 90 days of follow-up
	Days alive without mechanical ventilation within 90 days of follow-up
	Days alive without vasopressor/inotropic therapy within 90 days follow-up
	Days alive without RRT within 90 days follow-up
	Renal recovery at day 90

*ICU* intensive care unit, *RRT* renal replacement therapy, *SAR* serious adverse reaction

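### The experimental-arm definition of a protocol violation counts stopping fluid removal early, but not failing to start it or failing to move from furosemide to CRRT

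*Protocol article*

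**What the plan says.** Discussion, point 5, gives the reason for recording violations: "it is uncertain whether our intervention can be performed with the acceptance of the treating clinicians". It then defines them separately by arm: "protocol violations defined as the use of dialysis outside the recommended indications in the control group, and cessation of fluid removal", the latter applying to the experimental arm. In the control arm the violation is thus dialysis given outside the listed indications. In the experimental arm it is, in full, "cessation of fluid removal before fulfilment of safety criteria or achievement of neutral fluid balance in the experimental group".

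Table 1 makes this a secondary outcome: "Number of patients with one or more major protocol violations". The Abstract describes it as a number of violations, and Discussion point 5 as their frequency.

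The experimental strategy is set out under Forced fluid removal. It begins with a drug: "The first choice for fluid removal is diuretic therapy with furosemide which is continued for a minimum of 8 h". It then escalates: "If the therapeutic goal cannot be achieved and maintained by diuretic therapy it is replaced by fluid removal" by CRRT. Progress is checked on a fixed timetable: "The therapeutic effect is evaluated at three daily summary points on the ICU observation charts". The Resuscitation section adds a pause when a sign of inadequate circulation appears, and a restart once circulation has recovered.

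Under Monitoring and protocol adhesion, violations are entered in every patient's case form, and a violation leads to re-education of caregivers.

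**The concern.** An adherence measure should register the ways in which the assigned strategy can fail to be given. This one registers a single way, stopping too soon. A clinician who is uneasy about forced removal has two other easy courses: not to begin, or to leave the patient on furosemide that is not reaching the goal. Neither is a cessation, so neither is a violation.

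The Discussion lists physiological intolerance (point 1) and lack of adherence (point 5) as separate threats to feasibility, and the violation count is the outcome assigned to the second. If the day-5 difference is small and the count is near zero, the natural reading is that clinicians complied and physiology prevented removal. That reading could be wrong, and it would bear on whether a larger trial is pursued. In addition, re-education is tied to violations, so non-initiation and non-escalation would not trigger it while recruitment continues.

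**Working it through.** **Step 1. Compare the protocol's steps with the definition.**

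| Step required in the experimental arm | Section | Is failure a violation under Discussion point 5? |
|---|---|---|
| Start removal with furosemide | Forced fluid removal | No: nothing was begun, so nothing ceased |
| Replace furosemide by CRRT if the goal is not achieved and maintained | Forced fluid removal | No: removal is still running |
| Restart after a safety pause | Resuscitation | Unclear: the pause followed a met safety criterion, but never restarting can be read as ceasing before neutrality |
| Continue until neutral balance | Resuscitation | Yes |

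Two of the four failures are outside the definition, one is ambiguous and one is inside.

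**Step 2. Reproduce the plan's own figure.** Inputs from Statistical analysis: difference 6 L, SD 7.4 L, two-sided alpha 0.05, power 0.80. Allocation 1:1 is assumed, because no ratio is stated.

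- Normal approximation: n per arm = 2(1.960 + 0.842)² × 7.4² / 6² = 23.9, so 24 per arm and 48 in total.
- Two-sample t test: 24.88, so 25 per arm and 50 in total, as stated. Power at 25 per arm is 0.802.

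The sample size reproduces and is not in dispute.

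**Step 3. Illustrate what could go unrecorded.** Let a share f of experimental patients never start, or stay on ineffective furosemide, and get no more net removal than controls. Assume that full delivery gives 6 L and that the SD stays at 7.4 L. The expected difference is 6(1 − f). The document gives no value of f, so a range is shown.

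| f (assumed) | Expected difference | Power (t test, 25 per arm) |
|---|---|---|
| 0 | 6.0 L | 0.802 |
| 10% | 5.4 L | 0.715 |
| 20% | 4.8 L | 0.613 |
| 30% | 4.2 L | 0.503 |
| 50% | 3.0 L | 0.290 |

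In every row the experimental-arm count could be 0 of 25. The usual exact interval would then give a two-sided 95% upper limit of 1 − 0.025^(1/25) = 13.7%, which looks reassuring but excludes these failures by definition.

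**Step 4. Compare the wording of the outcome.** The Abstract counts violations, Table 1 counts patients with at least one major violation, and the Discussion refers to a frequency without the major qualifier. The unit (events or patients) and the severity threshold differ.

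**The case against.** **Non-delivery would be visible elsewhere.** This stands in part. The article commits to evaluating fluid and dialysis data in both arms (stated for bias), effect is charted three times daily, and Table 1 includes mean daily balance, time to neutral balance and days without renal replacement therapy. External monitoring of adhesion covers the first five patients per arm at each centre, so up to 3 × 5 = 15 experimental patients. A reader might infer that non-delivery would be undetectable; the documents do not support that. These data show that removal was small, but not whether the clinician declined or the patient could not tolerate it.

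**The full protocol or case form may list more.** This is possible, and the meaning of a major violation may be given there, so its absence from the article is not the complaint. But the article publishes a closed definition, and that definition should agree with any fuller one.

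**Definitions that differ by arm are legitimate.** This stands. The control arm has no protocolled intervention, so dialysis guidance is the main departure to record. A reader might infer that the plan compares unlike counts between arms, but no test of violation counts is stated.

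**Failure to restart is already covered.** This is arguable, so the table above marks it as unclear. It would be too strong to say that it never counts.

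**One patient's shortfall could exceed the 6 L target difference.** A reader might compute 1 mL/kg/h × 120 h = 8.4 L at 70 kg or 9.0 L at 75 kg. That is a single-patient upper bound: it assumes those weights, zero net removal, no pauses and enough overload not to reach neutrality before day 5. A 70 kg patient entering at the 10% threshold (7 L) reaches the ±1 L band after 6 L. Nor is it comparable with a difference in group means: among 25 patients, 8.4 L in one shifts the arm mean by 8.4 / 25 = 0.34 L. It is not relied on here.

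**Conclusion.** The point holds as a definition that does not match the protocol's own steps. Applied as written, an experimental patient in whom removal is never started, or in whom failing furosemide is never replaced by CRRT, counts as adherent; the status of a patient never restarted after a pause is unclear. A low violation count would therefore not show that clinicians accepted and delivered the intervention.

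The damage is limited to the interpretation of one secondary outcome and of the feasibility conclusion drawn from it. The primary outcome, the sample size and the treatment rules are unaffected. The power figures are illustrations under assumed non-delivery rates, 1:1 allocation, a constant SD and a full-delivery effect of 6 L; they are not predictions. The inconsistent unit and severity wording is a smaller defect in the same outcome. This is a cheap improvement worth making.

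**What to change.** 1. Extend the experimental-arm definition to count three further departures from steps the protocol already contains: removal not started, no replacement of furosemide by CRRT when the protocol's own condition for it is met, and no restart once the protocol's own condition for restarting is met. Take these conditions from the existing text and algorithm figures. No treatment rule changes.
2. Report violations by type within each arm.
3. Optionally, report the share of 8-hourly summary points, until neutrality, at which the goal was met or removal was in a protocol-permitted pause. This is an addition, not a correction.
4. Use one unit and one severity term for the outcome in the Abstract, Table 1 and the Discussion, consistent with any fuller definition in the full protocol or case form.

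The cost is a change of wording and some derivation from charts already read three times a day and case forms that already record violations. The downside is that the reported violation rate may be higher.
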